#### Qualitative data analysis

We will use an analytical strategy based on thematic content analysis to analyze qualitative data [45, 46]. Audio-recorded qualitative data, transcribed and with identifying information removed, will be analyzed using Nvivo. We will subject all data to an coding process guided by the Proctor Implementation Outcomes framework [47]. We will identify key themes and iteratively develop a coding scheme, organized according to key themes (i.e., barriers and facilitators to YRI delivery) and map key themes onto the Proctor Framework (i.e., feasibility, acceptability, adoption, appropriateness, sustainment) [47]. Two team members trained in coding scheme will independently code 10% of transcripts to examine reliability. Poor agreement (i.e., low kappa ratings as scored in the qualitative analysis program Nvivo) will be grounds for refining the coding scheme or retraining. Once all coding schemes demonstrate high reliability, team members will code the full qualitative dataset in Nvivo using the robust code books. Qualitative and quantitative implementation outcomes data will be synthesized and triangulated to understand barriers and facilitators to digital platform implementation as well as factors influencing adoption and “buy-in” of the platform within schools. We will integrate data from qualitative and quantitative sources using mixed methods “joint displays” to identify areas of convergence/divergence.

#### Cost-effectiveness analysis

We will conduct a cost-effectiveness analysis from a broad, societal perspective to estimate the social cost per QALY gained [24, 48]. Social cost factors all health costs stemming from an intervention, including the value of participants’ time, and is recommended by the Second Panel on Cost-Effectiveness in Health and Medicine for use in economic evaluations [49]. To estimate costs, we will use an ingredients approach in which activities are first identified as costs, and then the financial and economic costs of carrying out these activities are quantified [48]. Financial costs account for actual monetary expenses while economic costs encompass all resources, including those volunteered, and opportunity costs incurred by participants. Activities include staff and interventionist trainings, participant recruitment, session delivery, and review of work with supervisors. We will get cost estimates from a range of sources (e.g., invoices, receipts, budgets from implementation partners); staff time will be costed at full salary. All costs will be appropriately prorated to reflect actual effort or “real time spent”. We will request expenditure reports from partners to double check the ingredients-based costing approach and triangulate cost estimates. We will calculate the time invested by each YRI participant to derive a value of this time in dollars, based on median wages in Sierra Leone. All costs will be expressed in US dollars.

We will derive QALYs gained from the mental health impacts of the YRI supported by mobile supervision and standard supervision, measured using the EQ-5D-3L. We will convert EQ-5D-3L scores to QALYs. To generate QALYs from the EQ-5D-3L, we will calculate a summary index using a standard and relevant weighting scheme. In our case, the index scores will be converted to QALYs using weights developed for Zimbabwe [49]. We will track EQ-5D-3L scores across the duration of the study and derive the QALY difference between YRI with mobile supervision, YRI with standard supervision and control participants—an approach validated in previous studies. For the intervention to be cost-effective, each QALY gained must cost less than three times Sierra Leone’s gross domestic product at purchasing power parity [16, 50]; this follows standards for good value for money outlined in global health interventions [33, 51]. To extend our analysis beyond health to education, we will also estimate the cost per additional year of school enrollment.

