### Study aims

This study will implement the evidence-based YRI as an extracurricular resilience-building activity for youth in Sierra Leone’s secondary schools and train teachers to deliver the intervention. Teachers will receive either mobile phone-based supervision or standard in-person supervision to deliver the YRI. Mobile-based supervision will integrate WhatsApp with an mHealth app designed to support fidelity monitoring and feedback during supervision. Study aims are to: (a) examine the feasibility, acceptability, cost, and fidelity to the YRI delivered by teachers receiving mobile-based supervision compared with those receiving standard supervision; (b) compare the effectiveness of the YRI delivered in schools by teachers who receive either mobile-based supervision or standard supervision; (c) investigate potential mechanisms of YRI adoption and sustainment within schools, including readiness to change and organizational climate; (d) conduct a cost-effectiveness analysis to evaluate the relative costs vs. benefits of the YRI delivered in secondary schools with mobile-based supervision and standard supervision from a broad societal perspective, including educational outcomes.

We hypothesize that: (a) mobile-based supervision will be more feasible, acceptable, and cost-effective than standard supervision, and YRI fidelity scores for mobile supervision will be comparable to standard supervision; (b) youth mental health, emotion regulation, and daily functioning outcomes in mobile supervision will not differ from those in standard supervision over time; (c) readiness to change, organizational climate, and teacher buy-in will moderate YRI adoption and sustainment; (d) the YRI incremental cost-effectiveness ratio in both conditions will surpass the standard willingness to pay threshold [16].

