#### Data collection

Data collection will be at three levels: teacher, principal and youth. Teachers (*N* = 160) and principals (*N* = 40) will complete quantitative assessments on implementation-level outcomes at baseline and post-intervention. All principals and a subset of teachers (*N* = 40) will also complete qualitative exit interviews at post-intervention to explore key aspects of feasibility, acceptability, and adoption, (e.g., usefulness of YRI skill-building exercises), and internal and external factors that might influence facilitator experiences (e.g., school climate, incentives). The subset of teachers will be selected based on a multivariate sampling matrix [31, 32]. We will also explore feasibility and acceptability of mobile-based supervision via key informant interviews with facilitators who received mobile supervision at post-intervention.

Youth (*N* = 1200) will complete quantitative assessments on mental health and daily functioning at baseline and post-intervention. Youth from intervention schools (*N* = 960) will complete quantitative assessments on implementation-level outcomes. A subset of youth (from intervention schools; *N* = 32) randomly selected based on a multivariate sampling matrix will complete exit interviews at post-intervention to obtain their feedback on YRI feasibility, acceptability, and barriers/facilitators to adoption. We will also collect data on educational outcomes for all youth via administrative records (i.e., school attendance, grades, tardiness, disciplinary reports) at baseline, post-intervention and 12-month follow-up. All youth will complete the EQ-5D-3 L at baseline, post-intervention and 12-month follow-up to inform the cost-effectiveness analysis [33].

Trained RAs will administer assessments electronically via tablets. All classroom instruction, assignments and tests are completed in English in our catchment area, thus the Western region schools, assessments and interviews will be completed in English as a first option. Versions of all study assessments will also be available in Krio (the local language) for any participants indicating difficulties with English fluency or a preference for completing assessments in Krio. All measures have been forward and backward translated from English to Krio previously. We will report data disaggregated by sex.

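### The cost-effectiveness limit is set without a per-capita basis, hypothesis (d) points the opposite way to that limit, and costs and threshold are not tied to one price basis

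*Protocol article*

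**What the plan says.** Three statements in the Protocol article bear on this point.

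- **The rule.** Under Cost-effectiveness analysis, for the intervention to count as cost-effective, "each QALY gained must cost less than three times Sierra Leone’s gross domestic product at purchasing power parity". The text adds that this follows accepted value-for-money standards in global health and cites sources for it.
- **The measure and its currency.** The same section sets out "to estimate the social cost per QALY gained". It states "All costs will be expressed in US dollars". Participant time is costed so as to "derive a value of this time in dollars, based on median wages in Sierra Leone". Other inputs are invoices, receipts, partner budgets and staff salaries.
- **The hypothesis.** Under Study aims, hypothesis (d) is that "the YRI incremental cost-effectiveness ratio in both conditions will surpass the standard willingness to pay threshold".

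The Study design section explains that control schools are needed chiefly for this analysis, because they supply the reference QALY level.

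**The concern.** The rule is what turns the cost and QALY data into a verdict, and three things about it do not fit together.

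First, the limit is a multiple of gross domestic product with no per-capita basis, here or anywhere else in the article. A cost per QALY is a cost for one person-year of full health. Three times a whole country's output is not a limit that can separate good value from poor value.

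Second, the rule asks for a ratio below the threshold, while hypothesis (d) predicts one above it. Taken at its word, a result that confirms the hypothesis is a result that fails the rule.

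Third, the cost side is in US dollars and the limit is at PPP. No conversion is stated to put them on the same basis.

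At stake is aim (d), the main stated reason for enrolling 10 control schools and 240 youth. Its findings are meant to reach ministries and other policy makers.

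**Working it through.** The article gives no GDP, population, PPP factor, expected cost or expected QALY gain, so there is no figure of the plan's own to reproduce. The check covers direction and units, with labelled assumptions for scale.

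**1. Direction.** Write ICER for the social cost per QALY gained and L for the threshold.

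- Rule (Cost-effectiveness analysis): cost-effective if ICER < L.
- Hypothesis (d) (Study aims): ICER > L in both conditions.

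Both concern the same ratio, and the two inequalities exclude each other.

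**2. Size of the limit as written.** With N youth and a gain of q QALYs each, the total gain is N × q. The rule is missed only if incremental cost is at least 3 × GDP × N × q. N = 960 is the number of intervention youth (Data collection section); q is assumed.

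| Assumed q per youth | Total QALYs (960 × q) | Cost needed to miss the limit (3 × total), in national GDPs |
|---|---|---|
| 0.001 | 0.96 | 2.88 |
| 0.01 | 9.6 | 28.8 |
| 0.05 | 48 | 144 |

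For one intervention arm of 480 youth at q = 0.01, the total is 4.8 QALYs and the break-even cost is 3 × 4.8 = 14.4 national GDPs. None of this requires a population figure.

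**3. Comparison with a per-capita limit.** The two limits differ by a factor equal to the population, P. The article gives no population; P = 5 to 10 million is assumed. At q = 0.01 the break-even cost per youth, in units of GDP per capita, is:

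- as written: 3 × P × q = 3 × 5,000,000 × 0.01 = 150,000, up to 3 × 10,000,000 × 0.01 = 300,000;
- per capita: 3 × q = 3 × 0.01 = 0.03.

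**4. Price basis.** Let k be GDP at PPP divided by GDP at market exchange rates. If costs are in market-rate dollars and the limit is three times GDP per capita at PPP, the effective limit is 3 × k times market-rate GDP per capita. The article does not give k. Over an assumed range:

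| Assumed k | Effective multiple (3 × k) |
|---|---|
| 1.5 | 4.5 |
| 2 | 6 |
| 3 | 9 |
| 4 | 12 |

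If the dollars are already PPP-adjusted (international) dollars, the two sides agree and this step has no effect.

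**The case against.** The best defence is that these are wording slips in a condensed article. The text calls the threshold standard and cites sources for it, an analyst is unlikely to compare a cost per QALY with national output, and *surpass* was probably meant as clearing the bar. Hypothesis (a) and the Discussion both anticipate favourable cost-effectiveness. Exchange basis and price year are details that an article commonly leaves to a fuller plan.

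Much of this is fair as to intent. It does not rescue the text. The rule and the hypothesis are both stated, and as stated the first sets a limit that cannot discriminate and the second runs against it. The defence has most force on currency, where the article is silent rather than wrong.

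It also rules out several stronger readings that a reader might infer:

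- *That any finite cost passes, or that the rule can never fail.* Three times national GDP is a finite limit, and a zero or negative QALY gain would not satisfy a limit on the cost of each QALY gained.
- *That the two sides are certainly in different units.* The article does not say whether its dollars are market-rate or PPP-adjusted, and the values of k above are assumptions.
- *That the article sets two competing decision rules, or expects the YRI to be poor value.* Only the Cost-effectiveness analysis section defines a verdict; hypothesis (d) is a prediction, badly worded.
- *That a mobile-versus-standard ratio would break down because hypothesis (b) expects no outcome difference.* The article names no such ratio. Hypothesis (d) speaks of the YRI in each condition, and the control schools provide the reference.

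**Conclusion.** The point holds in three parts of unequal strength.

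- The opposite direction of hypothesis (d) and the rule is a firm contradiction within the article.
- The missing per-capita basis is probably a slip, but the stated limit is wrong as a decision rule: no realistic programme with a positive QALY gain could fail it. The break-even costs of 2.88 to 144 national GDPs rest on assumed gains of 0.001 to 0.05 QALY per youth.
- The price basis is conditional. If costs are in market-rate dollars, a per-capita limit at PPP is too lenient by k, a ratio the documents do not supply. If they are in international dollars, there is no mismatch.

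That per capita is the intended unit is an inference from the text describing the threshold as standard; the cited sources were not available to confirm it. Only aim (d) is affected. Sample size, power, and the fidelity and youth-outcome analyses do not depend on it.

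**What to change.** In Cost-effectiveness analysis, state that the YRI is cost-effective if its incremental cost-effectiveness ratio versus control is below three times Sierra Leone's GDP per capita. State also that costs and threshold are in the same currency unit and price year, either both in market US dollars or both in international dollars. The authors should confirm the per-capita multiple against the sources they cite.

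In Study aims, change *surpass* to *fall below* in hypothesis (d).

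The cost is a wording change in two places and, if needed, one currency conversion. The downside is a less lenient pass mark. No data collection changes. The Trial status section reports that youth recruitment had not begun at submission, so at that stage the correction could still have preceded any youth outcome data. It should in any case be made before the cost-effectiveness data are analysed, so that the price basis is not chosen once the ratio is known.

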### Dissemination

Study leaders are committed to the timely dissemination of research outcomes. The data generated in this study will be presented at national and/or international conferences and published in a timely fashion. All final peer-reviewed manuscripts that arise from this proposal will be submitted to the digital archive PubMed Central. For data that is de-identifiable, we will make data available in accordance with the National Institute of Health guidelines and the IRB.

Our study team will also explore multi-pronged strategies to disseminate findings, such as policy briefs, newspaper articles, radio announcements, and social-media site postings of study findings to target multiple audiences through multiple modalities, including key stakeholders and policy makers (e.g., Ministry of Basic and Senior Secondary Education, Ministry of Youth Affairs). We will provide stakeholders with resources to support adoption and sustainment of the YRI aided by mobile-based supervision after we complete our evaluation, such as mHealth app user resources and evidence briefs that can be shared with government stakeholders across ministries.

## Discussion

This study seeks to conduct a hybrid type 3 implementation-effectiveness cluster randomized trial to evaluate a new implementation strategy: mobile-based supervision for teachers delivering an evidence-based mental health intervention in Sierra Leone’s secondary schools and compare this strategy with standard, in-person supervision for teachers delivering the intervention. Research findings have the potential to expand the reach of evidence-based mental health services through a teacher workforce and open-source platforms. Training teachers to deliver evidence-based mental health interventions within public and open government subsidized schools has the potential to reach a larger population of vulnerable youth. Leveraging low-cost technology can improve the efficiency, effectiveness, and scalability of evidence-based mental health services in Sierra Leone as well as in other LMICs and resource-constrained settings and help offset the financial and human resource burdens associated with traditional modes of performance monitoring and quality improvement cycles. The mobile tools, if feasible and acceptable, could be modified to support teacher training, teaching quality, and adherence to the school curriculum. They also have the potential to support further scale-out and sustainment of the YRI throughout schools across other regions of Sierra Leone and West Africa more broadly, which could ultimately help to reduce the mental health treatment gap in this region.

Despite the potential cost-effectiveness results that we anticipate from using mobile-app supervision, sustainability remains a persistent challenge for implementation in LMICs due to limited financial, human and material resources. This could be addressed by engaging multiple stakeholders from the grassroots to the government level. We plan to engage the MBSSE, Sierra Leone’s Teaching Service Commission, and both in-country and international nongovernmental organizations to determine how best to sustain the program afterresearch funding has ended. Via these conversations, we hope to collaborate in co-creating a strategy to support YRI sustainability and to facilitate the capacity building necessary to bridge implementation gaps and increase sustainment of evidence-based practice.

### Trial status

At the time of manuscript submission, we had recruited and enrolled principal and teacher participants. Preparations were underway to begin youth participant recruitment.

## Data Availability

Not applicable; Data collection described in this study protocol has not started.

## Abbreviations

LMIC: Low-and middle-income country
YRI: Youth Readiness Intervention
MBSSE: Ministry of Basic and Senior Secondary Education
RA: research assistant
QALY: Quality adjusted life years
WHODAS: World Health Organization Disability Assessment Schedule
DERS: Difficulties in Emotion Regulation Scale
HSCL: Hopkins Symptom Checklist
EQ-5d-3L: EuroQual-5 Dimension
ICC: Interclass Correlation
